## Objective one

The occurrence of early post-operative complications of euthyroidectomy under the two arms (LA and GA) of the study will be measured by total occurrence of a particular complication divided by the total number of euthyroidectomy done under LA and GA, respectively. These will be expressed as percentages with 95% confidence interval and the difference in proportions will be compared using a two-sample Student’s *t*-test, assuming normal distribution and equal variance. The Shapiro–Wilk test will be used to assess for normalcy of distribution whereas Levene’s test will be used to assess for equality of variance.

For the pain scores, visual analogue scale will be stratified as no pain (0), mild (1–3) or moderate (4–6), and severe (7–10) and the difference in proportions will be compared using non-parametric Kruskal–Wallis rank sum test (H). The overall occurrence of adverse events in both groups will be summarized as proportions in accordance with Clavien Dindo classification [27].

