Previous studies comparing euthyroidectomy under LA versus GA have shown mixed findings with regard to the benefits and post-operative outcomes. Other than overcoming the need to book for intensive care space and an anesthesiologist [14], which most patients in low-income countries cannot afford in the case of thyroidectomy under GA [15], LA has been associated with less post-operative pain, costs, hospital stay duration, post-operative nausea, vomiting, throat discomfort, and voice changes [9, 16, 17]. According to research in Nigeria [13], India [8], and USA [16], complications such as hematoma, surgical site infection, and colloid occur in less than 4% of cases of thyroidectomy performed under LA. In a randomized controlled study in Germany [9], the occurrences of post-operative complications (pain, nausea, vomiting, throat discomfort, painful swallowing, voice change, and difficulty in breathing were less in the group of patients who underwent thyroidectomy under LA as compared with those under GA in contrast to the prospective study in Uganda [18]. According to the USA [16] and Ugandan [18] studies, GA is also more associated with persistent hypothyroidism although the Kenyan cross-sectional review showed no difference[11].

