### Primary outcome measures

The primary outcome measures will be early 30-day post-operative complications (harms), including: pain, nausea, vomiting, hematoma, transient voice changes, and surgical site infection rates.

The complications will be reported verbally to nursing or to attending physicians for evaluation and recorded on a questionnaire in accordance with MedDRA® version 4.21 standardized reporting on medical and surgical procedures. The post-operative pain will be measured based on visual analogue scale of 0–10 where 0 means no pain and 10 means the worst possible pain. The pain will be assessed at an interval of 6, 12, and 24 h and at 30 days. The mean pain scores will be compared at using Student’s *t*-test, assuming normal distribution; otherwise, medians will be compared using non-parametric Kruskal–Wallis rank sum test.

The nausea and vomiting will be reported to nursing or attending physicians and recorded to the questionnaire using a nausea score on a scale of 0–9 where 0 means no symptom and 9 means very severe. The symptoms will be assessed at an interval of 6, 12, and 24 h and at 30 days. The mean nausea scores will be compared using a paired Student’s *t*-test, assuming normal distribution; otherwise, medians will be compared using non-parametric Kruskal–Wallis rank sum test.

Complications: hematoma, transient voice changes, and surgical site infection rates will be assessed at 6, 12, and 24 h and at 30 days will be reported in accordance with the Clavien Dindo classification of surgical complications [27], where grade I represents complications that do not require any additional intervention, grade II requires pharmacological treatment but not radiological or surgical intervention for instance blood transfusion, grade III requires radiological or surgical re-intervention, e.g., neck exploration and hematoma evacuation, grade IV representing life-threatening complications with at least one organ dysfunction such as respiratory failure that requires intensive care admission. The difference in proportions will be compared using Wilcoxon sum rank test.

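### Yes/no complications are to be compared by a t-test conditional on a normality check that 0/1 data cannot pass, with no fallback and no link to the equivalence margin; pain has two unranked analyses

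*Protocol article*

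**What the plan says.** All of these outcomes are primary in the protocol article: pain, nausea, vomiting, hematoma, transient voice changes and surgical site infection.

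**Yes/no complications**
- Objective one defines occurrence as a simple proportion, "measured by total occurrence of a particular complication divided by the total number of euthyroidectomy done under LA and GA, respectively". It then states that "the difference in proportions will be compared using a two-sample Student’s *t*-test, assuming normal distribution and equal variance" and adds: "The Shapiro–Wilk test will be used to assess for normalcy of distribution whereas Levene’s test will be used to assess for equality of variance".
- Primary outcome measures deals with hematoma, voice change and infection, describes Clavien-Dindo grades I to IV, and ends: "The difference in proportions will be compared using Wilcoxon sum rank test".

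**Pain**
- Primary outcome measures: "The mean pain scores will be compared at using Student’s *t*-test, assuming normal distribution"; otherwise medians are compared by Kruskal–Wallis.
- Objective one cuts the same scale into categories, "visual analogue scale will be stratified as no pain (0), mild (1–3) or moderate (4–6), and severe (7–10"), and compares these by Kruskal–Wallis.

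Neither section says which analysis is the main one. The Introduction says that complications such as hematoma and surgical site infection "occur in less than 4% of cases of thyroidectomy performed under LA". The Sample size estimation section sets up an equivalence comparison of a dichotomous outcome with a 33% margin.

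**The concern.** A primary analysis should be one that can be carried out as written and that answers the design question. The plan for yes/no complications falls short on three counts.

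1. The t-test is tied to a normality check on data that take only two values. The scores for pain and nausea have a stated alternative if normality fails; the proportions have none.
2. The two sections name different tests for a difference in proportions in the same group of complications, and do not say whether one is meant for ordered grade and the other for occurrence.
3. Both are tests of difference. The trial is an equivalence trial, and a non-significant difference test does not show equivalence.

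For pain, two inferential analyses of the same measurements stand side by side without an order, so which one carries the conclusion is not fixed in advance.

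**Working it through.** **The plan's own figure.** Inputs from Sample size estimation: 83% (LA) and 79% (GA) without complication, margin 33 points, power 80%, type 1 error 0.05, 10% loss.
- One-sided 0.05 at the nearer margin: n = (1.645 + 0.842)² × (0.83×0.17 + 0.79×0.21) / (0.33 − 0.04)² = 6.18 × 0.307 / 0.0841 = 22.6, so 23 per arm; 23 / 0.9 = 25.6, so 26.
- One-sided 0.025 with 81% in both arms: (1.960 + 0.842)² × 2×0.81×0.19 / 0.33² = 7.85 × 0.3078 / 0.1089 = 22.2, so again 23 and then 26.

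The stated 26 per arm is reproduced. The design calculation concerns a difference in proportions set against a margin, whereas the analysis sections name only difference tests. Because both versions give 26, the figure does not settle whether the matching interval is 90% (0.05 each side) or 95% (0.025 each side).

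**Can the normality check be passed?** Shapiro–Wilk on 26 values, k of them events:

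| k | p |
|---|---|
| 1 or 25 | 7 × 10⁻¹¹ |
| 2 | 4 × 10⁻¹⁰ |
| 5 or 21 | 2 × 10⁻⁸ |
| 8 | 2 × 10⁻⁷ |
| 13 | 9 × 10⁻⁷ |

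Every split from 1 to 25 gives p < 0.000001. With 0 or 26 events the values are constant and the check has nothing to work on.

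**Can the t statistic be computed?** Assume a 4% rate in both arms (the Introduction gives under 4%, for LA only).
- Expected events per arm: 26 × 0.04 = 1.04.
- Chance of no event in either arm: 0.96⁵² = 0.120. The mean difference and the pooled variance are then both zero and t is 0/0.
- At 2% in both arms the chance is 0.98⁵² = 0.350; at 10% it is 0.9⁵² = 0.004.

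**Does it matter which of the two tests is used?** Two-sided p-values at 26 per arm:

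| Events | t-test | Wilcoxon (tie-corrected) | Fisher |
|---|---|---|---|
| 0 v 4 | 0.038 | 0.039 | 0.110 |
| 1 v 6 | 0.043 | 0.044 | 0.099 |
| 2 v 8 | 0.035 | 0.037 | 0.075 |

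Over all possible tables with equal true rates, the t-test and Wilcoxon disagree at 0.05 with probability 5 × 10⁻⁸ at 4%, 0.0002 at 10% and 0.008 at 19%.

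**Pain.** The protocol gives no standard deviation, so this is illustrative only: rounded scores on 0–10, mean 4, SD 2, 26 per arm. With a true 1-point difference, the score t-test and the four-category Kruskal–Wallis test disagree on significance in roughly one trial in seven. With no true difference, taking whichever is significant raises the false-positive rate from about 5% to about 7%.

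**The case against.** **The two sections may not conflict.** The Wilcoxon sentence follows directly on the Clavien-Dindo grades, which are ordered, and the article elsewhere speaks of proportions when it applies rank tests to ordered scales (pain strata, Likert satisfaction). On that reading one section ranks grades and the other compares occurrence. This reading is tenable, so a reader who infers a flat contradiction goes further than the text. What stands is that the sentence refers to proportions and does not say which variable it means.

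**A reader might infer that two tests allow the more convenient binary result to be picked.** The numbers do not support this: for rare events the two tests practically never disagree.

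**A reader might infer that the t-test distorts the type I error and that Fisher's test would cure it.** At 4% in both arms the t-test's actual size is 0.013, but Fisher's is 0.0004, further from 0.05. At 10% the sizes are 0.050 and 0.010. Size is therefore not the argument, and Fisher's test would be one more difference test.

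**A reader might infer that all the complications are rare.** The under-4% figure does not cover GA or voice change, and the planning rates imply 17% to 21% with any complication.

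**The t-test may be loose wording for a large-sample comparison of proportions.** That is possible, but Shapiro–Wilk and Levene's tests act on individual values, so the stated checks would still have to be removed.

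**The two pain analyses can coexist**, one as main and one as supportive, and a statistical analysis plan could rank them. That is fair. But the article itself states both as inferential comparisons of a primary outcome, and a few words would settle it.

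**Conclusion.** The point holds in a limited form. For yes/no complications, Objective one prescribes a t-test whose normality condition fails at every split of 26 values, with no alternative stated. The Wilcoxon wording in Primary outcome measures leaves its target unclear. The t statistic would be undefined in 12% of trials for a complication with a 4% rate in both arms; that figure rests on the assumption that GA shares the upper bound given for LA. None of the named tests addresses the equivalence question for which the trial was sized.

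The practical harm lies in the unworkable precondition and the missing link to the margin, not in selective choice between t-test and Wilcoxon. Room for choice exists mainly for pain, and under the illustrative assumptions it is modest. The sample size is not affected.

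**What to change.** Use the same wording in Primary outcome measures and Objective one:

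- **Each yes/no complication:** estimate the risk difference, LA minus GA, with a small-sample confidence interval (Newcombe or Miettinen–Nurminen), and read it against the plan's own 33-point margin. State the interval level that matches the intended alpha: 90% if 0.05 is spent on each side, 95% if 0.025. Any Fisher p-value is supportive only.
- **Delete** the t-test, Shapiro–Wilk and Levene steps for proportions.
- **Keep the Wilcoxon test** only for ordered Clavien-Dindo grade, and say so.
- **Pain:** name the 0–10 score comparison as the main analysis and report the four categories descriptively.

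The cost is wording and standard Stata commands. No new data and no change in sample size are needed. Whether a 33-point margin suits complications expected in only a few percent of patients is a separate question that this change does not settle.

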## Objective two

The cost of euthyroidectomy done under LA and GA will be estimated by the would-be expenditure on drugs and sundries based on national drug authority (NDA) quotation. The admission costs will be calculated in form of number days of admission (away from duty/work as cost) and bed occupancy for the two arms.

The average cost incurred on patients operated either under the LA or GA from admission till discharged will be calculated and compared. The difference in the average cost between the two arms will be compared using *t*-test, assuming normal distribution.

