### Interventions: modifications

#### Adverse events and trial discontinuation for individual participants

The participants are anticipated to experience pain discomfort and or other complications due to the surgery as the main treatment for goiter not because of the study. In addition to breach of trial protocols, too much pain during surgery using LA will result in converting to GA (cross over) and advancing to stronger analgesics other than prescribed in protocol with ultimate discontinuation of individual participant from the trial.

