### Randomization, blinding and allocation concealment and implementation

Patients who meet the inclusion criteria will be assigned randomly by research assistants to either local anesthesia group (L) or general anesthesia group (G) using envelope concealment. Half of these concealed envelopes will contain letter L and the other half letter G to represent LA and GA, respectively. Permuted balanced block randomization will be performed by the study supervisor to derive a random sequence of numbers that will represent the two arms in an allocation ratio of 1:1. The random sequence numbers will be generated using a web-based software (https://www.random.org/). A set of 52 numbers will be generated beginning with a minimum of 1 and maximum of 52. The numbers will then be used to label the sealed envelopes sequentially and will be concealed to research assistants. The content of the envelope will be concealed only to be opened in the operating room for the anesthesia providers to know what anesthetic technique is to be used for the research participant.

The study participants at this point in the operating room will not be blinded as the research and ethics committee considered it a moral obligation for patients to understand the nature and risks of anesthesia techniques to be used on them prior surgery.

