### Data management and analysis

Data will be coded, entered in Excel version 2016, and later exported to STATA 14.2. for analysis. The intention-to-treat model will be used to minimize bias as way of reflecting what happens in real clinical practice. The intention-to-treat population will be used for inference and will be defined as all eligible randomized patients recruited in this study. Analysis will be done per study objective. Socio-demographic and surgical factors will be summarized descriptively using summary measures as proportions, means, medians, and measures of variation such as standard deviations for means, interquartile range for medians. All analyses will be computed at 95% confidence intervals and regarding *p* < 0.5 as statistically significant.

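### The plan does not ensure that the cost of a failed local-anesthesia attempt stays in the LA arm: converted patients are discontinued and may be imputed, which can overstate the LA saving

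*Protocol article*

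**What the plan says.** Objective two in the protocol article describes the cost averages as follows: "The average cost incurred on patients operated either under the LA or GA from admission till discharged will be calculated and compared". The next sentence sets the test by arm: "The difference in the average cost between the two arms will be compared using" a t-test. The paragraph before it also gives "bed occupancy for the two arms". The randomization section ties the arms to the allocation list, a "random sequence of numbers that will represent the two arms in an allocation ratio of 1:1".

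The data management and analysis section sets the population: "The intention-to-treat population will be used for inference and will be defined as all eligible randomized patients recruited in this study". It adds "Analysis will be done per study objective" and makes no exception for cost.

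Two sections deal with conversion. Under adverse events and trial discontinuation for individual participants, "too much pain during surgery using LA will result in converting to GA (cross over"), and the participant is then discontinued from the trial. The section on individual discontinuation repeats this. The missing data section says that values will be imputed where end points are missing, and gives crossovers as an example beside withdrawals and losses to follow-up.

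The secondary outcome section takes cost and length of stay from the patients' case files.

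**The concern.** An LA patient who is converted has received the LA infiltration, then the GA drugs, and may stay longer. That expense is a consequence of choosing LA. A camp that adopts LA will pay it, so it belongs in the LA average.

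The population and the test point towards that treatment. The conversion rules point away from it: a discontinued participant may contribute no further data, and crossovers are named among those whose values are imputed. The description of the averages by the anesthetic patients were operated under does nothing to correct this. It leaves an analyst unsure where a patient who had both techniques is counted.

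Cost is one of three specific objectives, and lower cost is a main argument for LA in the abstract and the discussion. The patients whose handling is unclear are likely to be the most expensive in the LA arm, so losing their observed costs moves the result in one direction, towards a larger LA saving.

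**Working it through.** **Nothing to reproduce.** The protocol states no expected cost difference, standard deviation or conversion rate. The calculation below shows direction and rough size only.

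**Inputs**
- Mean cost under LA, L = US$65, and under GA, G = US$107.85 (Introduction, the Nepal study).
- Patients per arm, n = 26 (sample size estimation).
- Conversions, c = 3, range 1 to 5 (assumption: 3.8% to 19.2% of 26).
- Cost of a converted patient, K (assumption). Low case: K = G = 107.85. High case: K = L + G = 172.85. The high case is an upper bound, because the Introduction says the Nepal costs include operation and ward bed charges, and adding the two counts these twice.
- Imputation at the LA mean (assumption; the protocol article names no method).

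**Converted patients dropped, or imputed at the LA mean**

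The LA mean remains L, so the saving is G − L = 107.85 − 65 = US$42.85 for any c.

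**By allocated arm with observed costs**

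Saving = G − [(n − c)L + cK]/n

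- Low case (K = G): this reduces to 42.85 × (26 − c)/26.
- High case (K = L + G): this reduces to 42.85 − c × 107.85/26.

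| c | Low case, saving | Overstatement by 42.85 | High case, saving | Overstatement by 42.85 |
|---|---|---|---|---|
| 1 | 41.20 | 4% | 38.70 | 11% |
| 3 | 37.91 | 13% | 30.41 | 41% |
| 5 | 34.61 | 24% | 22.11 | 94% |

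For c = 3: 42.85/37.91 − 1 = 13% and 42.85/30.41 − 1 = 41%.

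**Dependence on the imputation.** If converted patients were imputed at the GA mean, c = 3 would give US$37.91. That is right in the low case and too high by 37.91/30.41 − 1 = 25% in the high case. The error therefore depends on how far the imputed value falls short of the true conversion cost. It is zero when the observed cost is used.

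**The case against.** The strongest reply is that the plan already settles the grouping. Intention-to-treat is the stated basis for inference with no exception for cost, the t-test compares the two arms, and the arms are defined by the random sequence. Describing patients by operation under LA or GA is also how this protocol names its arms: Objectives one and three use similar phrasing while speaking of arms.

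This reply stands against a stronger reading that a reader might infer from the description of the averages, namely that Objective two is an as-treated analysis in which every converted patient is costed to GA. No section says so. Under that reading, 3 conversions in the high case would give a saving of (26 × 107.85 + 3 × 172.85)/29 − 65 = US$49.57 against US$30.41 by arm, or 63% too large. That figure does not follow from the plan and should not be cited as its consequence.

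The reply does not remove the problem created by the conversion rules. Intention-to-treat fixes who is counted, but not whether a converted patient's observed cost is used. It can be said that a cost already in the case file is not missing and so would not be imputed. That is a reasonable reading, but the protocol does not state it. It says that converted patients leave the trial and gives crossovers as an example of participants to be imputed. The text permits the correct analysis without securing it.

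**Conclusion.** The concern holds in a limited form. The sections on population, conversion, missing data and cost do not fit together for LA patients converted to GA. Applying the stated discontinuation and imputation rules can take the observed cost of a failed LA attempt out of the LA average.

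On the illustrative inputs with 3 of 26 converting, the LA saving would be overstated by 13% if a conversion costs the GA price, and by 41% at the upper bound. Over 1 to 5 conversions the ranges are 4 to 24% and 11 to 94%. These sizes rest on an assumed conversion rate, on costs from another country, and on conversions being dropped or imputed at the LA mean. With no conversions the issue disappears. The direction is firmer than the size: whenever a conversion costs more than the value put in its place, the LA saving is too large. The change is worth making because it affects one of three specific objectives and is easily made.

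**What to change.** - In Objective two, define the averages over patients allocated to LA or GA, so that the description matches the test by arm that follows it.
- State there and in the missing data section that LA patients converted to GA stay in the LA arm for the cost analysis, with all their observed case-file costs (LA drugs, GA drugs and any added stay), and that these costs are not imputed.
- Reconcile the discontinuation passages with the intention-to-treat definition, so that discontinuation after conversion is not read as removal from the cost analysis.
- Cost by anesthetic actually received may be shown as a supplement, labelled as such.

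This takes a few sentences and needs no new data, since costs already come from case files. The drawback for the sponsor is that the reported LA saving may be smaller. The clinical rule on when a patient is converted is left as it is.
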